## Abstract

**Background:**

Exercise training has been shown to reduce angina and promote collateral vessel development in patients with coronary artery disease. However, the mechanism whereby exercise exerts these beneficial effects is unclear. There has been increasing interest in the use of whole genome peripheral blood gene expression in a wide range of conditions to attempt to identify both novel mechanisms of disease and transcriptional biomarkers. This protocol describes a study in which we will assess the effect of a structured exercise programme on peripheral blood gene expression in patients with stable angina, and correlate this with changes in angina level, anxiety, depression, and exercise capacity.

**Methods/Design:**

Sixty patients with stable angina will be recruited and randomised 1:1 to exercise training or conventional care. Patients randomised to exercise training will attend an exercise physiology laboratory up to three times weekly for supervised aerobic interval training sessions of one hour in total duration. Patients will undergo assessments of angina, anxiety, depression, and peripheral blood gene expression at baseline, after six and twelve weeks of training, and twelve weeks after formal exercise training ceases.

**Discussion:**

This study will provide comprehensive data on the effect of exercise training on peripheral blood gene expression in patients with angina. By correlating this with improvement in angina status we will identify candidate peripheral blood transcriptional markers predictive of improvements in angina level in response to exercise training.

**Trial Registration:**

Clinicaltrials.gov identifier: NCT01147952

## Background

Regular exercise protects against cardiovascular disease [1] and has beneficial effects on coronary perfusion and ventricular function in patients with established coronary artery disease [2]. However, the exact mechanism whereby exercise training exerts these effects is unclear. Meta-analyses have concluded that exercise based cardiac rehabilitation reduces cardiac mortality in patients with coronary artery disease (prior myocardial infarction, angina, bypass grafting or angioplasty) by 26%-31% [3,4]. Although exercise favourably influences serum lipids and blood pressure, the biological pathway whereby it protects against cardiovascular death remains unclear, though there is substantial evidence that exercise improves myocardial oxygenation. Exercise-induced improvement in myocardial perfusion has been demonstrated in a number of studies [2,5] suggesting exercise training increases absolute myocardial blood flow, rather than by altering myocardial efficiency. Exercise training has also been shown to improve coronary artery endothelial function (even after only 4 weeks training) [6].

Some of the favourable effects of exercise appear to be mediated by improvement in coronary collateral artery recruitment. Exercise training improves collateral vessel function, even in arteries with no coronary stenosis [7]. This is in keeping with epidemiologic evidence that in patients with coronary artery disease, collateral function is better in more active individuals [8]. Since better collateral vessel function is associated with improved survival [9], this is a plausible mechanism for the survival benefit seen with exercise. In keeping with real increases in myocardial perfusion, in one study exercise training has been shown to be better at improving angina than percutaneous coronary intervention [5].

Microarrays enable measurement of expression of almost all human genes in a small clinical sample simultaneously. This powerful technique has been widely applied in cancer, where the relevant tissue is usually easily available either through biopsy, or surgical removal. Application of such techniques is more difficult with heart disease, since the primarily affected organs (the heart itself or its supplying coronary arteries) cannot easily be sampled. However, white blood cells (leukocytes) play a major role in both the development of coronary artery disease [10], in development of collateral vessels [11] and peripheral blood is easily obtainable. Thus, the gene expression of peripheral blood (which reflects gene expression in leukocytes) may be informative in patients with or at risk of cardiovascular disease.

Previous studies have demonstrated the utility of measuring gene expression in peripheral blood or isolated cell types from peripheral blood in patients with cardiovascular disease. These studies found that gene expression in either unsorted peripheral blood [12] or isolated mononuclear cells [13] predicted the presence of coronary artery disease on coronary angiography. Interestingly, gene expression in peripheral unsorted blood accurately reflects expression of the same genes in atherosclerotic arteries [12]. These observations support the validity of peripheral blood as a surrogate of arterial gene expression. This utility exists either because infiltrating leukocytes contribute to arterial gene expression signatures, or pro-atherosclerotic influences alter both arterial and leukocyte gene expression in a similar fashion.

In keeping with the central role of circulating leukocytes (particularly monocytes) in collateral vessel development, microarray profiling of circulating monocytes is able to distinguish between patients with good compared with poor coronary collateral vessels [14,15].

One small previous study assessed the effect of exercise training on peripheral blood gene expression [16]. Five patients with metabolic syndrome exercised for 16 weeks, and significant differences in gene expression were detected in 11 biologic processes. No control group was used but this study does prove that exercise induces measurable changes in gene expression even in a small number of patients.

This study will determine the effect of exercise training on peripheral blood gene expression in patients with stable angina and correlate these changes with improvement in angina status and exercise capacity as a surrogate of myocardial perfusion. In addition, since anxiety and depression are highly prevalent among patients with coronary artery disease and exercise training has been suggested to improve this, [17] we will monitor the effect of our intervention on anxiety and depression.

## Methods/Design

### Study aims

The purpose of this original research is to characterise the effect of exercise training on angina status, anxiety, depression and the peripheral blood transcriptome, in patients with stable angina and coronary artery disease. Gene expression outcomes aim to provide an insight into the mechanism of the beneficial effects of exercise training in coronary artery disease and on collateral blood vessel development which might in turn provide evidence as to the impact upon cardiac morbidity in these patients.

### Study design & setting

This is a prospective randomised control comparison study. After completion of a baseline assessment, participants will be randomly assigned to either a structured exercise or a usual care control group. Patients will be randomised by an independent researcher via code numbers using nQuery software (nQuery Advisor 6.01, Statistical Solutions, USA). The randomisation sequence will not be not disclosed to the researcher responsible for the day-to-day running of the trial until patients have completed baseline assessments. It is not possible to blind participants or investigators to treatment allocation, but data collected will be blinded prior to analysis to eliminate bias. This research will be conducted in the Clinical Research Facility (CRF) at the Northern General Hospital, Sheffield, UK and the Centre for Sport and Exercise Science at Sheffield Hallam University, UK. The researchers involved are experienced clinicians and scientists. Ethical approval was obtained for this study through Bradford Research Ethics Committee.

### Patients

Patients with stable angina will be identified from cardiology clinics at Sheffield Teaching Hospitals NHS Foundation Trust, UK. Written, informed consent will be obtained from each potential volunteer before baseline assessment.

### Inclusion Criteria

1) Class I to III angina pectoris (classified according to the Canadian Cardiovascular Society [CCS]) with documented myocardial ischemia or coronary artery disease on angiography.

2) Ability to read and speak English to a level allowing satisfactory completion of written questionnaires and to understand instruction during the exercise programme.

3) Age 30-80 years of either sex.

### Exclusion Criteria

1) Acute coronary syndromes or recent myocardial infarction (< 2 months).

2) Left main coronary artery stenosis > 25% or high-grade proximal left anterior descending artery stenosis.

3) Known reduced left ventricular function (ejection fraction < 40%).

4) Significant valvular heart disease.

5) Insulin-dependent diabetes mellitus.

6) Occupational, orthopedic, and other conditions that preclude regular exercise.

7) Patients who's ECG prevents interpretation of an exercise test (LBBB, RBBB, pacemaker implantation).

8) Patients already performing greater than 30 min continuous exercise three times weekly (self-reported).

### Exercise intervention

Patients randomised to exercise training will attend an Exercise Science facility based at Sheffield Hallam University. This facility has a range of aerobic exercise equipment, including cycle ergometers, treadmills and cross-trainers. The intervention will comprise sessions of aerobic exercise training for 12 weeks total, up to three times weekly. An interval training regimen will be used, incorporating three minutes of exercise followed by one minute active recovery for 30 minutes total. Heart rate will be monitored throughout; ensuring patients do not exceed 85% of predicted maximum heart rate or 10 b.m^-1 ^below the angina threshold [1]. Individuals who were taking medication that alters maximum heart rate (e.g. beta blockers) will have their exercise intensity monitored using the Borg Ratings of Perceived Exertion [RPE] scale [18]. Exercise intensity in this instance will be set at that point just below the onset of angina. Each exercise session will be preceded by 10-15 minutes of light intensity/gentle mobility exercise and followed by a 10-15 minute period of cool-down activities. If angina is provoked during an interval, exercise will halt until angina subsides, either with rest or GTN treatment. If angina continues longer than 5 min the principal investigator or another clinically qualified investigator will be contacted to assess the patient. Once angina has subsided, blood pressure will be checked, and the intervals will restart at a heart rate 10 b.m^-1 ^below the level which caused the angina symptoms. Subsequent sessions may exceed this level of intensity if the angina threshold is found to have increased (due to exercise training adaptation or alteration of medication).

Hence, each supervised exercise session will last 50-60 minutes in total and patients will be encouraged to attend as many sessions as possible up to three times weekly over the 13 week period. Exercise frequency, intensity, duration and modality, as well as rate of progression, will be logged. After completing the first six weeks, participants will have a week break in training (during which visit 3 takes place), so that acute gene expression changes in response to exercise do not confound the analysis.

### Outcome measures

Outcome measures will be performed at CVBRU at baseline, midpoint (week 7), endpoint (week 14), and 6 month follow up. At assessment visits patients will have fasted for at least 12 h. On arrival, the following blood tests will be obtained; full blood count (FBC), fasting glucose (FG), fasting lipids (Lip), and peripheral blood RNA (RNA). The patients will then be offered a light meal. They will complete two questionnaires: The Seattle Angina questionnaire (SAQ), and the Beck Depression/Anxiety Inventory (BDI). The questionnaires are well established, widely used and well validated tools for assessing these outcomes [19-21]. In addition a full drug history will be obtained (DH). Height and weight will also be recorded (H&W). Following completion of these questionnaires, an exercise tolerance test will be performed (ETT) to give an indication or aerobic exercise tolerance and assess angina threshold. RNA samples (stored in a HTA licensed Biorepository) will be extracted and used to bind to Affymetrix Human Genome HU133 microarrays to assess whole genome peripheral blood gene expression. See Figure 1 for study flow diagram.

**Figure 1 F1:**
[figure not shown]
**Flow diagram indicating participant's involvement throughout the course of the study**.

### Sample size calculation

As our primary outcome measure is gene expression in whole blood, *a priori *sample size calculations are not possible. Based on the pilot study guidelines of [22], we will recruit 30 volunteers for each group, making a total sample size of 60. The results of this pilot will provide information on recruitment, compliance and attrition, and will identify logistical constraints that might limit the number of potential recruits. Variability data for the outcome measures and estimates of the treatment effect could be used to inform design a subsequent larger-scale randomised controlled trial, if post hoc analysis reveals this initial study to be underpowered.

### Statistical analysis

Outcomes will be compared at each assessment point using a mixed-design factorial ANOVA. Where any significant difference existed at baseline between groups, ANCOVA procedures will be implemented, with baseline values used as the covariate [23]. Statistical significance will be set at *p *< 0.05. Bivariate relationships between exercise tolerance and other outcome variables will be evaluated using Pearson's correlation analysis. Data will be analysed using SPSS (SPSS U.K. Ltd, Woking U.K.). The data will be analysed on an intention to treat basis with all analyses including missing data by imputing change across time to be zero. Parametric data will be presented as mean differences of change scores between time points, with 95% confidence intervals and effect sizes (calculated as Cohen's *d *i.e. mean of the treatment effect divided by the standard deviation of the controls). Gene expression data will be analysed using our previously published probabilistic method for analysis of microarray data that improves probe level sensitivity [24-26].

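### The clinical outcomes have no named test of the intervention: a four-visit ANOVA and visit-by-visit comparison are combined at 0.05, and neither is tied to week 14

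*Protocol article*

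**What the plan says.** Under Statistical analysis, the protocol article says "Outcomes will be compared at each assessment point using a mixed-design factorial ANOVA" and then "Statistical significance will be set at *p *< 0.05". Baseline enters as a covariate only if the arms differ significantly at baseline. Results are to be shown as differences in change scores with confidence intervals, but no pair of time points is singled out. Gene expression has its own method, so in practice the ANOVA sentence governs the clinical outcomes.

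Outcome measures lists the visits as "baseline, midpoint (week 7), endpoint (week 14), and 6 month follow up". The abstract places the last one "twelve weeks after formal exercise training ceases". Under Sample size calculation, gene expression is the primary outcome, the study is called a pilot, and "we will recruit 30 volunteers for each group, making a total sample size of 60".

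**The concern.** The ANOVA sentence joins two different procedures. A mixed-design ANOVA of two arms over four visits yields a group main effect and a group-by-time interaction, each drawing on all visits. Comparison at each assessment point means separate between-arm tests. The section does not say which of these answers whether training worked, and gives no rule for several visits.

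The choice could therefore be made after the output is seen. Depending on it, the end-of-training effect is tested with an inflated error rate or, in many plausible settings, with less power than the same data allow. With 30 per arm there is little power to spare. The sample size section also intends the treatment-effect estimates to inform a larger trial.

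**Working it through.** **Inputs from the protocol article.** 30 per arm, allocated 1:1; level 0.05 (sidedness not stated, two-sided assumed); one baseline and three post-baseline visits. The sample size has no effect size, SD or power behind it, so the only figure to reproduce is 2 × 30 = 60, which agrees.

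**Assumptions not in the documents.** Unit SD at each visit, no missing data, within-patient correlation ρ from 0.3 to 0.8 and constant over time, week 14 effect 0.7 SD. The week 7 effect is 0.35 SD, or 0.7 in the flat pattern. The 6-month effect is 0, 0.35 or 0.7 SD.

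**Step 1: visit-by-visit reading, no true effect.** For three independent tests, 1 − 0.95³ = 0.143. The visits are correlated, so the rate was also simulated (10,000 trials per scenario). The chance of at least one p < 0.05 per outcome was 10.2-13.4% for raw values, 12.1-12.5% for change scores and 12.7-13.8% for baseline-adjusted values. This step needs no assumed effect.

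**Step 2: group main effect.** It tests the mean of the four between-arm differences, and the expected baseline difference is zero:
- effect gone by 6 months: (0 + 0.35 + 0.70 + 0)/4 = 0.26 SD
- half remaining: (0 + 0.35 + 0.70 + 0.35)/4 = 0.35 SD
- persisting: (0 + 0.35 + 0.70 + 0.70)/4 = 0.44 SD
- flat from week 7: (0 + 0.70 + 0.70 + 0.70)/4 = 0.53 SD

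**Step 3: group-by-time interaction.** It does not average visits; it responds to any departure from parallel profiles. With 30 per arm its non-centrality is 15 × Σ(Dj − D̄)² / (1 − ρ) on 3 degrees of freedom, where Dj is the between-arm difference at visit j. The week 14 change contrast has 15 × 0.7² / [2(1 − ρ)] on 1 degree of freedom. At ρ = 0.5:
- half remaining: Σ = 0.245, giving 15 × 0.245/0.5 = 7.35 on 3 df
- gone, or persisting: Σ = 0.337, giving 15 × 0.337/0.5 = 10.1 on 3 df
- week 14 change contrast: 15 × 0.49/1 = 7.35 on 1 df

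Under partial fade the interaction spreads the same 7.35 over three degrees of freedom and loses power. Under full fade or persistence its larger non-centrality makes up for the extra degrees of freedom.

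**Step 4: simulated power, %, at ρ = 0.3 / 0.5 / 0.7.**

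| Effect at weeks 7, 14 and 6 months (SD) | Group main effect | Interaction | Week 14 change | Week 14, baseline-adjusted |
|---|---|---|---|---|
| 0.35, 0.7, 0 | 31 / 24 / 21 | 60 / 76 / 94 | 62 / 76 / 94 | 80 / 87 / 96 |
| 0.35, 0.7, 0.35 | 49 / 39 / 33 | 45 / 60 / 85 | 61 / 76 / 94 | 80 / 86 / 96 |
| 0.35, 0.7, 0.7 | 67 / 56 / 47 | 59 / 76 / 94 | 61 / 76 / 93 | 79 / 87 / 96 |
| 0.7, 0.7, 0.7 | 82 / 72 / 63 | 63 / 79 / 96 | 61 / 76 / 93 | 79 / 86 / 96 |

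At ρ = 0.8 the interaction (96% or more) and the adjusted contrast (99%) barely differ, and the main effect has 20-58%. One cell favours the main effect: a flat effect at ρ = 0.3 (82% against 79%), where averaging removes enough noise to offset the dilution.

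**Step 5: how much is baseline adjustment.** With effects of 0.3, 0.6 and 0.3 SD, correlation 0.6 decaying with time and a Greenhouse-Geisser correction, power is 50% for the interaction, 27% for the main effect, 72% for the week 14 change contrast and 81% for the adjusted contrast. Of the 31 points between 50% and 81%, 72 − 50 = 22 come from using one contrast and 81 − 72 = 9 from adjusting for baseline.

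**The case against.** A reader might infer that the visit after training stops dilutes the week 14 effect in any omnibus test. The figures do not support that. When the effect has gone entirely by 6 months, the interaction nearly matches the week 14 change contrast. The loss is clear under partial fade. It can also appear under persistence if correlations decay over time: with effects of 0.3, 0.6 and 0.6 SD and correlation 0.5, 53% against 63%. The documents say nothing about how the effect behaves after training.

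A reader might also infer that the group main effect is the planned treatment test. The text does not say so, and its reporting by change scores points elsewhere. The dilution in Step 2 applies only if that term is chosen.

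Three further points have force. Week 14 is already labelled the endpoint, although there it pairs with midpoint as a visit label and the analysis section ties no test to it. The clinical outcomes are not primary and the study is a pilot, so strict error control across visits is less pressing. A condensed article may leave the exact contrast to an analysis plan that is not shown. Against the last point, the article states a method and a threshold, and an analysis plan faithful to that sentence would inherit its ambiguity.

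**Conclusion.** The point holds in limited form. The stated method does not identify which term or visit tests the intervention.

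- **Error rate:** unadjusted visit-by-visit testing gives about 10-14% per outcome instead of 5%. This is the firmest figure.
- **Power:** the interaction is generally below a baseline-adjusted week 14 contrast, by 26 points at ρ = 0.5 under half fade (60% against 86%) and by little or nothing at high correlations. The main effect is usually far below it, with the one exception shown. These sizes depend on assumed effects, correlations and complete data, and part of the gain belongs to baseline adjustment.

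The primary gene-expression analysis is not affected. Priority is moderate.

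**What to change.** State under Statistical analysis that the principal clinical comparison for each outcome is the between-arm difference at week 14, adjusted for baseline in all cases, taken as one contrast from the repeated-measures model. Report week 7 (early response) and 6 months (persistence) as supportive, with confidence intervals. State that neither the omnibus interaction nor the group main effect is the test of the intervention.

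This takes a few lines of text and no new patients, visits or data. The small cost is less emphasis on week 7 and 6 months.

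### Clinical outcomes are adjusted for baseline only if a baseline significance test rejects, so chance selects the model and most outcomes lose the covariate's precision

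*Protocol article*

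**What the plan says.** The Statistical analysis section of the protocol article sets the default: "Outcomes will be compared at each assessment point using a mixed-design factorial ANOVA". It then gives one condition for using baseline as a covariate: "Where any significant difference existed at baseline between groups, ANCOVA procedures will be implemented, with baseline values used as the covariate". The same section sets the significance level at 0.05 and gives no separate level for the baseline test. It says that parametric results will be reported as between-group differences in change, with 95% confidence intervals and a standardised effect size. Gene expression is sent to a separate, previously published probabilistic method.

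Under Study design & setting, the order of events is clear: "After completion of a baseline assessment, participants will be randomly assigned to either a structured exercise or a usual care control group". Under Sample size calculation: "we will recruit 30 volunteers for each group, making a total sample size of 60". Under Outcome measures, the visits are listed: "Outcome measures will be performed at CVBRU at baseline, midpoint (week 7), endpoint (week 14), and 6 month follow up". Each outcome therefore has its own baseline value by design.

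**The concern.** The reason to adjust for a baseline value is that it predicts the follow-up value. Whether the arms happen to differ significantly at baseline says nothing about that. Under randomisation the null hypothesis of the baseline test is true by design, so a rejection is a chance event. The rule therefore lets chance decide, outcome by outcome, which model is fitted.

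Two things are at stake for angina, anxiety, depression and exercise tolerance. First, nearly every outcome gives up precision that the trial has already paid for by measuring baseline. Second, when a moderate imbalance does occur, the rule usually leaves it without ANCOVA, so the estimate from that particular trial is off by a predictable amount. Both matter with 60 patients, all the more because the protocol hopes to use the effect and variability estimates to design a larger trial.

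**Working it through.** **Inputs from the protocol.** 30 per arm, 60 in total (2 × 30 = 60); 1:1 randomisation after baseline; significance level 0.05. The sample size comes from pilot-study guidance, so there is no power figure to reproduce.

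**Assumptions.** Two-sided tests, with 0.05 also used for the baseline test. Baseline to follow-up correlation ρ of 0.5 to 0.8. A treatment effect of 0.6 SD. Normal data with equal SDs, one baseline and one follow-up. Neither ρ nor the effect is in the document, and the planned model has four assessments, so the power figures are illustrations.

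**Step 1: when the rule triggers.** The smallest baseline difference that reaches p < 0.05 is t(0.975; 58) × √(2/30) = 2.002 × 0.2582 = 0.517 SD. A 0.5 SD imbalance gives t = 0.5/0.2582 = 1.94, p = 0.058, and no ANCOVA. Under randomisation the trigger fires for 5% of outcomes. With four clinical outcomes, the chance that at least one switches model is 1 − 0.95⁴ = 18.5% if they are independent, and less if they are correlated.

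**Step 2: variance.** In units of the follow-up variance, the factors are 1 for follow-up values, 2(1 − ρ) for change scores and 1 − ρ² for ANCOVA. Relative to ANCOVA, follow-up values therefore cost 1/(1 − ρ²) and change scores cost 2/(1 + ρ).

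**Step 3: bias given a 0.5 SD imbalance without ANCOVA.** Follow-up values: +0.5ρ. Change scores: −0.5(1 − ρ), the opposite sign, because subtracting the whole baseline over-corrects through regression to the mean.

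| ρ | Variance vs ANCOVA: follow-up | Variance vs ANCOVA: change | Bias: follow-up | Bias: change |
|---|---|---|---|---|
| 0.5 | 1.33 | 1.33 | +0.25 SD | −0.25 SD |
| 0.6 | 1.56 | 1.25 | +0.30 SD | −0.20 SD |
| 0.7 | 1.96 | 1.18 | +0.35 SD | −0.15 SD |
| 0.8 | 2.78 | 1.11 | +0.40 SD | −0.10 SD |

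**Step 4: simulated power of the rule** (40,000 trials per setting, 30 per arm, effect 0.6 SD; the rule uses ANCOVA if the baseline test rejects and the default otherwise). Repeat runs agree to about one percentage point.

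| ρ | Rule, change-score default | Rule, follow-up default | ANCOVA always |
|---|---|---|---|
| 0.5 | 64% | 64% | 74% |
| 0.6 | 73% | 64% | 80% |
| 0.7 | 85% | 64% | 89% |
| 0.8 | 95% | 65% | 97% |

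**Step 5: simulated error rates with no effect.** Overall type I error of the rule is about 3.5-4.5% for ρ of 0.5 to 0.7, falling to about 3% at ρ = 0.8 with follow-up values. Averaged over randomisations, bias is zero within simulation error. About 12.5% of outcomes have a non-significant imbalance above 0.35 SD. Among those, type I error is about 6-9% with change scores and 9-13% with follow-up values, against about 5% for ANCOVA.

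**The case against.** The strongest defence is that the mixed ANOVA already uses baseline. It has baseline among its time points, and the results are to be presented as differences in change. On that reading it is wrong to say that imbalances go uncorrected, and that part of the defence stands: they are over-corrected. They are uncorrected only if follow-up values are compared visit by visit, which the wording about each assessment point also allows. On either reading the estimate is less precise than ANCOVA and biased given the imbalance. With change scores the loss shrinks as ρ rises and nearly vanishes at 0.8 (95% against 97% power).

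A reader might also infer that the rule inflates false positives or biases the trial's estimates in general. It does neither. Overall type I error is slightly below 5% and the estimate is unbiased over repeated randomisations. The raised error rates in Step 5 apply only to the roughly one outcome in eight with a sizeable non-significant imbalance.

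A third inference would be that the primary analysis is compromised. The protocol names gene expression as primary and analyses it by a separate method whose details are not in the document. Nothing shows that the baseline-test rule reaches it.

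Finally, this is a self-described pilot with no power claim. That lowers the stakes but does not justify the rule, since a pilot meant to supply effect and variability estimates gains from a model fixed in advance.

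**Conclusion.** The concern holds for the clinical outcomes. The rule is written into the protocol, its trigger carries no information under randomisation, and about 95% of outcomes forgo a covariate already collected. Under the assumptions above, always adjusting gains about 10 percentage points of power at ρ = 0.5 on either reading (74% against 64%). At ρ = 0.8 the gain is about 2 points with change scores (97% against 95%) and about 32 points with follow-up values (97% against 65%). The size depends on ρ and on which contrast of the ANOVA is meant, and the document settles neither.

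The 0.52 SD threshold and the 5% trigger rate do not depend on ρ. They follow from 30 per arm, randomisation and a two-sided 0.05 test. This is a matter of efficiency and pre-specification that should be fixed. It is not a threat to overall validity or, on what is shown, to the primary analysis.

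**What to change.** Delete the baseline significance test. For every continuous clinical outcome, pre-specify an ANCOVA, or a repeated-measures model, with that outcome's own baseline as a covariate whatever imbalance is observed. Take baseline out of the time factor, so that the week 7, week 14 and 6-month follow-up values are the responses. Report baseline-adjusted differences with 95% confidence intervals.

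No new data are needed. In the single follow-up case the cost is one residual degree of freedom (58 to 57). The sentence on presenting change scores must be aligned with the new model, and the zero-change rule for missing data must be restated for it (a missing follow-up value set equal to baseline). The change should be made before outcome data are examined, since the defect is that the data choose the model. No change to the gene-expression method is proposed.

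### Zero-change imputation as the only missing-data method biases the group difference and weakens its confidence interval unless patients with missing data truly did not change

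*Protocol article*

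**What the plan says.** The Statistical analysis section of the protocol article puts the analysis on an intention-to-treat footing and gives one rule for missing values: "all analyses including missing data by imputing change across time to be zero". It describes no alternative method and no sensitivity analysis. Results are to be given as "mean differences of change scores between time points, with 95% confidence intervals and effect sizes", with the effect size defined as the "mean of the treatment effect divided by the standard deviation of the controls". Gene expression data are assigned, in a separate sentence, to a published microarray method.

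The Sample size calculation section sets the size ("we will recruit 30 volunteers for each group, making a total sample size of 60") from pilot-study guidelines, without a power calculation. It treats dropout as something to be learned: "The results of this pilot will provide information on recruitment, compliance and attrition". It also gives the results a later use: "Variability data for the outcome measures and estimates of the treatment effect could be used to inform design a subsequent larger-scale randomised controlled trial", should this study prove underpowered.

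**The concern.** The rule is single imputation of one fixed value. It raises three problems.

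- **Bias.** A patient with no follow-up value counts as a patient who did not change. If such patients would in fact have changed, their arm's mean is pulled toward zero. When both arms change and one loses more patients, the two means are pulled by different amounts, which can create or distort a difference.
- **Precision.** The filled-in zeros enter the analysis as if measured. They add to the sample size and usually reduce the spread, so standard errors are too small for what was observed.
- **Later use.** The SD and the effect estimate are what the article offers for planning a larger trial, and both depend on the amount of missing data.

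Unequal dropout is plausible here. Allocation is open, and only the exercise arm is asked to attend supervised sessions up to three times a week for 12 weeks.

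This is a stated analysis choice, not a detail left to a fuller document. Intention to treat means keeping patients in their randomised arm; it does not require this imputation.

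**Working it through.** **Inputs from the article:** 30 patients per arm; significance level 0.05, taken as two-sided to match the 95% intervals; outcome expressed as the difference in mean change.

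**Assumptions, because the article gives no figures:** change-score SD of 1; true effects around 0.8 SD; dropout of 10%, 20% and 30%, or unequal; data missing completely at random; zero change meaning no change from baseline. The article states no effect, SD or power, so it has no figure of its own to reproduce.

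**1. Expected estimate.** With mean changes μE (exercise) and μC (control) and dropout dE and dC, the zero-imputed difference has expectation

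(1 − dE)·μE − (1 − dC)·μC.

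With equal dropout d this is (1 − d) times the true difference. For a true 0.8 SD:
- 10%: 0.9 × 0.8 = 0.72
- 20%: 0.8 × 0.8 = 0.64
- 30%: 0.7 × 0.8 = 0.56

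**2. Coverage and power.** Simulation of 40,000 trials per scenario, with a pooled t interval on change scores at one visit, true effect 0.8 SD and unchanged controls:

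| Equal dropout | Zero imputation: estimate | Coverage | Power | Observed data: estimate | Coverage | Power |
|---|---|---|---|---|---|---|
| 10% | 0.72 | 94% | 81% | 0.80 | 95% | 82% |
| 20% | 0.64 | 89% | 76% | 0.80 | 95% | 77% |
| 30% | 0.56 | 80–81% | 69% | 0.80 | 95% | 71% |

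At 20% dropout the mean interval width is 0.95 with imputation and 1.16 with observed data, so the interval is narrower around a biased centre. The power loss is only 1–2 points because the estimate and its standard error shrink together. It is larger if only the exercise arm loses patients: at 20%, 71% against about 82%.

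**3. Unequal dropout.** No true treatment effect, both arms changing by 0.5 SD, dropout 10% in one arm and 30% in the other:

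0.9 × 0.5 − 0.7 × 0.5 = 0.45 − 0.35 = 0.10 SD in favour of the arm that lost fewer patients.

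Simulated type I error is about 7%; observed-data analysis stays at 5%. If the shared change is 1.0 SD, the false difference is 0.20 SD and type I error about 12%. With a real effect (changes of 1.0 and 0.5, true difference 0.5):
- exercise 10%, control 30%: 0.9 × 1.0 − 0.7 × 0.5 = 0.55
- exercise 30%, control 10%: 0.7 × 1.0 − 0.9 × 0.5 = 0.25

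**4. SD for later planning.** With a proportion m imputed and mean change μ, the variance becomes (1 − m)(1 + m·μ²). For unchanged controls and m = 0.20 this is 0.80, an SD of √0.80 = 0.89 (about 0.88 as the average sample SD in simulation). Sample size for a fixed difference scales with the variance, so a trial planned on that SD would be about 20% too small. With μ = 1 the variance is 0.80 × 1.20 = 0.96, an SD of 0.98. The understatement is therefore usual but not universal, and large mean changes can reverse it.

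**The case against.** The strongest objection concerns the missing-data mechanism. The figures above assume that patients with missing values would have changed as much as the others. In an exercise trial, those who stop may never gain, or may lose, the benefit. If dropouts truly have zero mean change, the effect among all randomised patients is 0.72, 0.64 and 0.56 SD at 10%, 20% and 30% dropout. Zero imputation then recovers it with coverage of about 95%. Under that mechanism it is the observed-data analysis that is wrong: it gives 0.80, with coverage of about 94%, 92% and 88%. This stands. A reader might infer that every reported estimate, interval and SD must be wrong; the documents do not support that, since they say nothing about why data will be missing. What remains is that the article relies on this one assumption alone, untested.

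Other objections also stand in part:

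- **Wording.** Zero change could mean no change since the last observed visit. A patient seen at week 7 would then keep that change at week 14, and the (1 − d) factor would apply in full only to patients with no follow-up. The effect would be smaller.
- **Effect size.** With unchanged controls the dividing SD shrinks too. Mean Cohen's d falls to about 0.78, 0.74 and 0.70, against 0.82–0.83 from observed data, which is less than the raw shrinkage.
- **False differences.** These need both a shared non-zero change and markedly unequal dropout. With no mean change and 30% against 10% dropout, type I error stays at 5%. If the exercise arm loses more patients while both arms improve, the bias runs against exercise.
- **Gene expression and correlations.** A reader might infer from the reference to all analyses that whole arrays will be set to no change, or that artificial zero pairs will inflate the correlations. Neither is stated. Expression data have their own method, and the article does not say that Pearson's correlation will be applied to change scores, although the study aims suggest it. These points call for clarification only.
- **Pilot status.** The article says its estimates could, not will, inform a later trial. This lowers the stakes but does not remove them.

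**Conclusion.** The concern holds in limited form. The plan commits to zero-change single imputation as its only missing-data method. Unless patients with missing data truly did not change, the group difference is biased. The imputed values are also treated as data, the SD offered for later planning is usually too small, and intervals cover below their nominal level.

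The size depends on assumed attrition. At 10% equal dropout the effect is small (0.72 for a true 0.8, coverage 94%). At 20–30% it is material (0.64 to 0.56, coverage 89% to 80–81%). A large loss of power should not be inferred when dropout is equal. These figures rest on data missing completely at random, change measured from baseline, SD 1 and 30 per arm; a different mechanism or the last-visit reading would reduce them. Because the article treats attrition as unknown, the method should not depend on its being negligible. The point should be fixed, but it does not invalidate the design.

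**What to change.** For the clinical outcomes, make a likelihood-based mixed model for repeated measures the main analysis. It should use all observed visits of all randomised patients, with arm, visit, arm-by-visit interaction and the baseline value. Keep zero-change imputation as a labelled sensitivity analysis, and say whether zero change is counted from baseline or from the last observed visit. State that zero-change values are not imputed for missing arrays and are not used in the correlation analyses.

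The cost is wording only, and SPSS, the package the article names, fits such a model. The downside is that the main analysis then relies on data being missing at random; the retained zero-change analysis shows how far the conclusions depend on that.
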